**University of Auckland**

**[name] PhD**

**Department of Biochemistry**

**University of Otago**

The genome-wide association studies (GWAS) of serum urate and fractional excretion of uric acid (FEUA) have consistently reported a strong association with common variants of *SLC2A9* and *ABCG2* [4-8]. The Genetics of Gout in Aotearoa study has strongly implicated the *SLC2A9* gene in development of gout in Māori and Pacific people (odds ratios  $\geq 5.0$ ) [9]. Variation in the *rs11942223* *SLC2A9* single nucleotide polymorphisms (SNP) was most strongly associated with gout in Māori, Pacific and Caucasian case-control cohorts in this study. Between 31.7%-47.2% of control participants possessed at least one protective alleles (i.e. 1/2 and 2/2 genotypes)

*ABCG2* encodes the cellular efflux pump breast cancer resistance protein (BCRP). An *ABCG2* variant (*rs2231142*, *Q141K*) is strongly associated with gout and hyperuricaemia, and is thought to regulate serum urate concentrations through extra-renal (gut) underexcretion [10]. In addition, *ABCG2* variants play a role in treatment responses to allopurinol (a purine xanthine oxidase inhibitor), and BCRP can transport allopurinol [11].

Our recent studies of acute fructose loading have shown that *SLC2A9* and *ABCG2* variants influence changes in serum urate, serum glucose changes and fractional excretion of uric acid (FEUA) in response to a fructose load [12, 13]. It is unknown whether these effects occur due to direct interactions with fructose, or whether these effects are non-specific responses to hyperuricaemia induced by fructose. Here, we aim to examine the role of *SLC2A9* and *ABCG2* variants on serum urate responses and renal urate handling in response to an acute inosine load.

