### 6.3. Visit 2: study visit summary

At the study visit, a venous catheter will be inserted for blood collection. Following an overnight fast, subjects will consume the inosine tablets (1.5g, Source Naturals Inosine) with 500ml water between 0800 and 0900. Blood will be obtained for urate, creatinine, and serum storage, prior to ingestion and then 15 minutes, 30 minutes, 60 minutes, 120 minutes, and 180 minutes after ingestion. Blood will also be obtained for DNA extraction at baseline. Urine volume will be measured and urine will be obtained at these time points (with the exception of 15 minutes post-ingestion) for testing of urate and creatinine. Participants will remain otherwise fasted for the remainder of the study visit and will be given a light meal after removal of the intravenous catheter.

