### **9.2. Statistical Methods**

Data will be presented as mean (SD) or median (IQR) for descriptive purposes. Measures of effect will be presented with the appropriate 95% confidence interval. The primary analysis will be a comparison of the hyperuricaemic response to an inosine challenge in the entire group (n=100), based on the presence or absence of the *rs11942223* protective allele. Secondary and exploratory analyses will be comparison of the hyperuricaemic response to an inosine challenge based on subgroup analysis (within each ancestral subgroup), and based on other clinical features, such as age, sex and BMI in the entire group.

A key secondary analysis is the effect of the *ABCG2 Q141K* risk variant on the serum urate and FEUA response to an inosine challenge.

Data will be analysed using a mixed models approach to repeated measures where the dependent variable, change from baseline, will be examined in an analysis of covariance. Main effects of allele presence/absence, time and their interaction will be constructed and the baseline value of the dependent variable will be included as covariate. Significant group effects will be explored using the method of Tukey to preserve an overall 5% significance level. All analyses will be performed using SAS (SAS Institute Inc v 9.4) on an intention to treat basis. All tests will be two-tailed.

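### The 9.2 model gives baseline a single slope for all post-dose times; because the groups are genotypes tied to baseline urate and FEUA, any drift in that slope would leak into the time-specific allele effects and the allele-by-time test

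*Protocol*

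**What the plan says.** Protocol 9.2 sets out a repeated-measures mixed model in which "the dependent variable, change from baseline, will be examined in an analysis of covariance". It then names the terms: "Main effects of allele presence/absence, time and their interaction will be constructed", and "the baseline value of the dependent variable will be included as covariate". The only interaction with time is the one for allele.

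The primary comparison in 9.2 is "based on the presence or absence of the" *rs11942223* protective allele. The groups are therefore defined by genotype and not by randomisation. The background text before the Primary Hypothesis reports that genome-wide studies of "serum urate and fractional excretion of uric acid (FEUA) have consistently reported a strong association with common variants of" *SLC2A9* and *ABCG2*, the two genes under study.

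Section 6.3 schedules post-dose blood at "15 minutes, 30 minutes, 60 minutes, 120 minutes, and 180 minutes after ingestion". Urine follows the same schedule, "with the exception of 15 minutes post-ingestion". Urate thus has five post-dose values and FEUA four.

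**The concern.** A single baseline coefficient assumes that change depends on baseline equally at every sample. Early on, little of the response to inosine has developed; by 180 minutes much more has. The dependence on baseline may differ between those times, and the protocol offers no reason to think it constant.

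In a randomised trial a wrong common slope costs little, because the arms share an expected baseline. Here the protocol's own rationale predicts that they do not. The between-group part of the misfit then appears as an allele effect that varies with time. At stake are the allele-by-time test, which 9.2 names, and allele effects at single times such as 180 minutes, the time used in the subgroup power statement in 9.1. Section 9.2 describes no other model for FEUA or for the key secondary *ABCG2* analysis, so the point carries over to both.

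**Working it through.** **The plan's figures.** The plan gives no number on this point. Section 9.1 supplies three inputs: 70 versus 30 participants, an SD of change of 0.03 mmol/L at all times, and a target difference of 0.02 mmol/L. Its 90% power recomputes to about 86%: the standard error is 0.03 × √(1/70 + 1/30) = 0.00655, and Φ(0.02/0.00655 − 1.96) = 0.863. That is a separate matter and does not bear on this one.

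**Assumptions not in the documents.** Within-group baseline SD is 0.07 mmol/L. The correlation between successive samples is 0.8, first-order autoregressive in sample order. The baseline slope moves linearly in minutes from 0 at 15 minutes to −0.1 or −0.2 at 180. Carriers start 0.02 to 0.06 mmol/L lower. There is no true allele effect given baseline.

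**Formula.** False allele effect at time t = (b_t − b_common) × D. Here D is the baseline difference between allele groups (carriers minus non-carriers) and b_common = (1′S⁻¹b)/(1′S⁻¹1), with S the covariance of the changes.

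**Central case: slope to −0.2, D = −0.04.**
- Slopes at 15, 30, 60, 120 and 180 minutes, from −0.2 × (t − 15)/165: 0, −0.018, −0.055, −0.127, −0.200.
- With constant SD, the first and last samples have weight 1 and the three middle ones 1 − 0.8 = 0.2, a total of 2.6.
- b_common = [0 + 0.2 × (−0.018 − 0.055 − 0.127) − 0.200]/2.6 = −0.240/2.6 = −0.092.
- Bias at 180 minutes = (−0.200 + 0.092) × (−0.04) = +0.0043 mmol/L, about 22% of 0.02.
- Averaged over the five times, the mean slope is −0.400/5 = −0.080, so the bias is (−0.080 + 0.092) × (−0.04) = −0.0005 mmol/L.

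**Range, constant SD 0.03.** Rejection rates are from simulation.

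| Slope at 180 min | Gap (mmol/L) | Bias at 180 min (mmol/L) | Allele-by-time rejection, model as written |
|---|---|---|---|
| −0.1 | 0.02 | 0.054 × 0.02 = 0.001 | about 5% |
| −0.2 | 0.02 | 0.108 × 0.02 = 0.002 | about 7% |
| −0.2 | 0.04 | 0.0043 | about 12% |
| −0.2 | 0.06 | 0.108 × 0.06 = 0.0065 | about 20% |

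With baseline-by-time in the model, rejection returns to about 5%. The test of the time-averaged allele effect stays at about 5% to 6% with the common slope.

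**Steeper drift.** A separate simulation used slopes of 0, −0.05, −0.10, −0.20 and −0.30 and a correlation of 0.6. With an unstructured covariance, allele-by-time rejected in 8%, 23% and 51% of runs at gaps of 0.02, 0.04 and 0.06; with compound symmetry, in 12.5%, 34% and 68%. With no gap (5.6% to 6.1%) or a constant slope (3.5% to 5.6%) there was no material inflation. With the added term, rates were 4% to 6%. The time-averaged test stayed at 4% to 5.4%.

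**SD growing from 0.01 to 0.03** (slope to −0.2, gap 0.04). The early samples now dominate b_common. The bias is about 0.008 at 180 minutes and 0.003 on average, and the time-averaged test rejects in 12% of runs or somewhat more.

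**The case against.** The strongest objection is that the drift is assumed. No section says the baseline slope changes over time. Regression to the mean from measurement error in the baseline enters every change score from the first sample, so that part of the slope is roughly constant and harmless. The baseline gap is likewise not given in mmol/L. This stands: the mechanism is shown, its size is not.

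A second objection is that the form of a covariate is often left to the statistical analysis plan, which might add the term. That carries less weight, because 9.2 lists the model terms and writes a time interaction for allele only.

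A third is that the error rates depend on the estimand. With slope −0.2 and gap 0.04, the unadjusted mean change at 180 minutes really does differ between genotypes by 0.2 × 0.04 = 0.008 mmol/L. The excess is false only for the baseline-adjusted effect. Since 9.2 adjusts for baseline, that is the relevant reading, but it should be stated.

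Three stronger readings are tempting and not supported:
- A reader might infer that the overall allele comparison is biased. Under the constant SD of 0.03 in 9.1 it is essentially unaffected; that harm needs an SD that grows with time. The constant SD comes from fructose data, so growth under inosine is open but not shown.
- A reader might infer that all drift in the slope is counted as allele-by-time. Only the part multiplied by the between-group baseline difference is; the rest goes to the residual.
- A reader might treat 180 minutes as a designated test. In 9.1 it serves the sample-size argument only.

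**Conclusion.** The point holds in limited form. As written, the 9.2 model has one baseline slope, and the protocol's own background gives reason to expect different baselines by allele group. If the slope drifts, the baseline-adjusted allele effects at single times are biased and the allele-by-time test loses its 5% level. Over the assumed range the bias at 180 minutes runs from 5% (0.001/0.02) to about 32% (0.0065/0.02) of the target difference, and the low end does no visible harm to the test. The direction is as uncertain as the size: it follows the sign of the drift and of the gap. In the central case it would make carriers look more responsive at 180 minutes and so would mask the hypothesised effect. No size was worked out for FEUA or *ABCG2*. This is a cheap improvement to a stated model, not a demonstrated error in the primary comparison.

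**What to change.** In 9.2, list the terms as allele, time, allele-by-time, baseline and baseline-by-time, for serum urate and FEUA and for both *SLC2A9* and *ABCG2*. Report the allele effect overall and at each time from that model.

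The cost is 5 − 1 = 4 degrees of freedom for urate and 4 − 1 = 3 for FEUA, with 100 participants measured repeatedly. No new data are needed, and little is lost if the slope proves constant.

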## 10. APPROVALS

Ethical approval for the study will be obtained from the Multi-Regional Ethics Committee (MREC) prior to commencement of the study. All patients will provide written informed consent prior to participation in the study.

## 11. STUDY PROTOCOL SUMMARY

| Visit No.                                           | 1      | 2     |
|-----------------------------------------------------|--------|-------|
| Visit type                                          | Screen | Study |
| Informed consent                                    | √      |       |
| Inclusion/exclusion criteria                        | √      |       |
| Laboratory tests (eGFR, urine pH testing)           | √      |       |
| Confirm fasting status                              |        | √     |
| Relevant medical history recorded                   |        | √     |
| Detailed family history recorded                    |        | √     |
| Ancestry recorded                                   |        | √     |
| Weight, height, waist circumference                 |        | √     |
| Blood pressure                                      |        | √     |
| Insert venous catheter                              |        | √     |
| Baseline blood and urine testing, including for DNA |        | √     |
| Administer inosine tablets                          |        | √     |
| Serial blood and urine testing                      |        | √     |
| Remove venous catheter                              |        | √     |
| Record adverse events                               |        | √     |

